**Observation and record**

Primary outcome measures

Pain scale

Secondary outcome measures

1. Side effects related to PCA
2. Overall press times and total dose

Randomization and allocation, 30 subjects each group

Blind

Observer and nurse

Only enrollment number

Low dose

High dose

Moderate dose

Sufentanil 2μg/kg + Tropisetron 10mg to 100ml

Sufentanil 2.5μg/k + Tropisetron 10mg to 100ml

1. Observational measures

General measures

Basic data includes age, height, body weight, gender, occupation, education, diagnosis, surgery type, disease history, allergy history, vital sign, preoperative ECG，blood routines, urine routines, liver and renal function, medication and anesthetics.

Time data collection includes surgery time (from the start of incision to the complete of the last stich), anesthesia time (from induction to discontinuation of maintenance), time to open eye and time to extubation.

Clinical measures

The clinical outcomes include pain scores VAS and NRS at each time-point, side effects related to PCA, and use of the PCA.

1. Adverse events

The adverse events in the study are defined as severe respiratory depression needs mechanic ventilation and severe sedation.

1. Data collection

Data establishment

Criterion of data record

The patient case and case record as the original data can’t be changed. If there is a necessary to modify the case, don’t change the original one, but instead provide an explanation of the reason. Check the abnormal value or value out of normal range, and provide an explanation by the investigator as well.

Traceability

All the cases of the participants should be recorded completely and in time no matter of eliminated case or case fell off. All the original tests should be pasted in the research cases. The research cases should be preserved safely.

Data locking

The database is locked by researcher, applicant, analyzer, supervisor after confirm of the correction of data. The data file can’t be modified after locking. Problems discovered after locking should be reconfirmed and modified in process of analyzing.

Data quality

The supervisor is in charge in supervision of the study periodically to ensure the study is compliant to the protocol, GCP and local laws and regulations. This includes on site check of the completeness, clearness of the CRF, cross check with the original record and clarification some management issues.

The investigators should be relative fixed. Study and discuss the protocol and brochure. Get consensus of opinion in methods of data collection and measurement.

File record

Recorded data in CRF should be traceable from original case, otherwise input in the CRF directly. At the latter circumstance, the CRF will be seen as original data. The data needed checking should be recorded well. Research files and all original data should be conserved well.

1. Statistical analysis

The aim of the study was to determine the optimal dose of sufentanil PCIA after moderate surgery with most pain relief. The expected standard deviation of means was 15 mm h, and standard deviation of subjects was 45 mm h of VAS. The significance level was set at 0.05 and the power at 0.8. Then the calculated sample size was 30 patients each group. Patient characteristic data (height, weight, age, laboratory test data, anesthesia duration, surgery duration, drugs consumptions) were compared by analysis of variance (ANOVA). Patient gender, surgery type were compared by Chi-square analysis. Comparisons of VAS or NRS for pain were performed with repeated-measures ANOVA. Ranked data as sedation degree and vomiting and nausea scale were analyzed with the Kruskal–Wallis tests. Probability values under 0.05 were considered significant.

1. Appendix

Visual analogue scale (VAS) of pain

From no pain (=0) to worst pain imaginable (=10). Patients are encouraged to draw a stroke across the 10 cm line. The distance from “0” to the stroke is record as pain score.

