The patients are eligible to be randomized provided the surgery duration within 4 hours. The eligible patients will be assigned to one of three treatment arms (A, B, C) through the table of random numbers based block randomization stratified by enrollment sequence. Each block contains 6 patients and there must be 2 patients in each block assigned to A treatment, 2 assigned to B treatment and 2 assigned to C treatment. Fifteen groups of permutation and combinations were combined based on the table of random numbers generated by a statistician. The allocation sequence is according to the sequence of surgery.

1. Blind

The allocation mark is sealed in a sequentially numbered envelope one each till 30 min before the end of surgery. The envelope will be then unsealed by the nurse who is responsible for the preparation of the pump. The observer is another investigator who is blind to the allocation. The nurse and observer must not communicate about the patient’s medication or analgesic effect. The pump has no label on except the enrollment sequence number.

1. Patient population

The patients with no gender limit aging from 20 to 75, BMI 18 to 28 kg/m^2, American Society of Anesthesiologists (ASA) grade I to II, anticipated surgery duration within 4 hours and agreed to sign consent paper are scheduled for selective moderate surgery including abdominal surgery (gastrectomy, colectomy, and rectectomy for cancer). Women participants in the study have to be menopause or use routine contraceptive method.

Patients with known allergy or contradiction to the treatment drugs, or severe respiratory, cardiovascular or neurological disease, hepatic or renal dysfunction, psychiatric history or unstable mental state are excluded from the study. Patients with a history of drug or alcohol abuse, chronic use of opioids and pregnant or breast-feeding will be excluded as well.

1. Study group

The participants are randomly allocated to three groups as following: low dose group (sufentanil 1.5μg/kg), moderate dose group (sufentanil 2.0μg/kg) and high dose group (sufentanil 2.5μg/kg)

1. Anesthesia

Preoperative

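### The 80% power holds only if all 90 randomised patients are analysable: 30 per arm is the bare calculated number, and classically run repeated-measures ANOVA can lose further patients

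*Protocol*

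**What the plan says.** The Statistical analysis section of the protocol gives the sample size inputs as "The expected standard deviation of means was 15 mm h, and standard deviation of subjects was 45 mm h of VAS", adds that "The significance level was set at 0.05 and the power at 0.8", and concludes: "Then the calculated sample size was 30 patients each group".

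The flow chart under Study route randomises the same number: "Randomization and allocation, 30 subjects each group". The Randomization section fixes the total. "Each block contains 6 patients and there must be 2 patients in each block assigned to A treatment", with two each to B and C, and "Fifteen groups of permutation and combinations were combined based on the table of random numbers generated by a statistician". I read this as 15 blocks of 6.

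No loss allowance is stated. The traceability paragraph under Data collection does contemplate lost cases, since records must be complete "no matter of eliminated case or case fell off".

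For pain, the plan states: "Comparisons of VAS or NRS for pain were performed with repeated-measures ANOVA". The clinical measures are VAS and NRS scores at each time-point. The protocol does not say what happens to a patient with a missed score.

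**The concern.** A calculation that returns 30 per arm returns the number needed in the analysis. If exactly that number is randomised, the stated power assumes that every patient contributes. A document that makes provision for eliminated and lost cases should not state 80% without that condition.

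The named method can widen the gap. Classical repeated-measures ANOVA works on patients with a complete set of scores, so one missed assessment removes the whole patient. The share of patients lost is then larger than the share of scores lost.

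There is also a possible bias. The arms differ only in sufentanil dose, and the background section names both inadequate analgesia and over-sedation as known problems. The VAS requires the patient to mark a line. If over-sedated or poorly controlled patients miss scores more often, an analysis of complete cases would leave out some of the patients who matter most for choosing a dose.

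**Working it through.** **Inputs from the protocol.** Three arms (k = 3); SD of the group means 15 mm h; SD of subjects 45 mm h; significance level 0.05; power 0.8; 30 per arm.

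**Total randomised.** 15 blocks × 6 = 90 = 3 × 30, so there is no spare block.

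**Reproducing the plan's figure.** The calculation fits a one-way ANOVA omnibus F test.

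- Effect size: f = 15/45 = 1/3.
- Noncentrality: λ = N × f² = 90 × 1/9 = 10.
- Degrees of freedom: k − 1 = 2 and N − k = 87.
- Power = P(noncentral F exceeds the 5% critical value) = 0.801.
- At 29 per arm (N = 87) power is 0.786, so 30 is the smallest equal number per arm that reaches 0.80.

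The match depends on the SD of the means being computed with divisor k. With divisor k − 1, f would be 0.272 and 80% power would need 45 per arm. The plan's 30 therefore rests on divisor k, which I use below.

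**Power after losses.** The formula is the same, with N the number analysable and losses spread evenly over the arms. The protocol gives no loss rate, so every row below the first is an assumption.

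| Analysable (N) | Lost | λ = N/9 | Power |
|---|---|---|---|
| 90 | 0 | 10.00 | 0.801 |
| 89 | 1 | 9.89 | 0.796 |
| 86 | 4 | 9.56 | 0.781 |
| 85 | 5 | 9.44 | 0.776 |
| 81 | 9 (10%) | 9.00 | 0.754 |
| 72 | 18 (20%) | 8.00 | 0.697 |

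Each lost patient costs about half a percentage point at first. The shortfall is about 2.5 points at five lost (0.801 − 0.776), 4.8 points at 10% (0.801 − 0.7535) and 10.4 points at 20% (0.801 − 0.697).

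**Scope of these figures.** They are the power of the protocol's own calculation, on a summary in mm h. They are not the power of the repeated-measures ANOVA of the individual scores, which the protocol's inputs do not allow one to compute.

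**The case against.** The strongest reply has four parts.

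**Missing-data rules.** These commonly sit in the SAP, which is not at hand. A reader might infer that the protocol prescribes a complete-case analysis. It does not. Listwise exclusion is a property of the classical method, and no such rule is written down. This part of the point is therefore conditional. What remains is that the protocol itself fixes the method, and its usual form has this weakness.

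**Size of the loss.** A reader might infer that the power claim collapses with the first lost patient. It drops below 0.80, but only to 0.796, and it is still 0.781 after four. Randomisation is also late: surgery must be within 4 hours, and the envelope stays sealed until 30 minutes before the end of surgery. Many exclusions therefore fall before allocation. That stands, but it does not cover losses during postoperative scoring.

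**Extrapolated losses.** One can take six assessments, each missed independently 3% or 5% of the time, and obtain 0.97⁶ = 0.833 or 0.95⁶ = 0.735 of patients complete, a loss of 17% or 26%. The number of assessments, the miss rates and the independence are all assumed. Misses that cluster within patients would remove fewer patients. The documents do not support these as expected losses, and I do not rely on them.

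**Bias.** A reader might infer that missingness will follow dose. The documents make this plausible but do not show it, and the traceability sentence forecasts no rate of lost cases. Nor is sphericity a general objection: the between-arm main effect does not depend on it. It affects the time and arm-by-time tests, for which standard corrections exist.

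**Conclusion.** The point holds in a limited form. The number randomised equals the bare calculated number with no reserve, so the 80% is conditional on all 90 patients being analysable. A few losses matter little. The shortfall becomes material from about five patients (0.776) and reaches 0.754 at an assumed 10% loss and 0.697 at an assumed 20%. These figures assume a one-way F test on the mm h summary, f = 1/3 and even losses across arms.

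The choice of repeated-measures ANOVA adds an avoidable risk: as classically run it discards patients with partial data, and it could bias the dose comparison if missed scores are related to dose. The size of that risk cannot be derived from the protocol. The sample size arithmetic is correct and reproduces, and nothing here invalidates the trial. The change is worth making because it is cheap.

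**What to change.** 1. Replace repeated-measures ANOVA of the pain scores with a linear mixed model for repeated measures: fixed effects for arm, time and arm-by-time, unstructured covariance, and Kenward-Roger degrees of freedom. Include all randomised patients with any pain score.
2. Estimate the time-weighted (mm h) differences between arms from that model, with the weights taken from the assessment times, so that the analysis addresses the quantity used in the sample size calculation.
3. State the 80% as conditional on 30 analysable patients per arm, with about 0.75 if 10% of patients give no usable score.

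The model keeps patients with isolated missed scores. It relies on missingness being explained by the observed data, so it reduces the risk of bias but does not remove it if missed scores depend on the unrecorded pain itself.

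The cost is slightly more analysis work and a slightly less favourable stated power, with no extra patients. If the sponsor would rather protect the 80%, the alternative is to inflate: for an assumed 10% loss, 30/0.9 = 33.3, rounded up to 34 per arm, which is 102 patients or 17 blocks of 6 (12 more patients).

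### The protocol collects operation type, age and sex but names no covariate for the pain analysis, giving up precision at no saving

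*Protocol*

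**What the plan says.** Under Patient population, the protocol enrols adults aged 20 to 75 of either sex for "abdominal surgery (gastrectomy, colectomy, and rectectomy for cancer"). Under Observational measures, age, gender and surgery type are among the basic data to be recorded.

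Under Randomization, patients are allocated to three arms by "block randomization stratified by enrollment sequence". Blocks have six patients, two per arm. No patient or surgical characteristic is a stratum.

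Under Statistical analysis, continuous characteristics, age among them, are compared by ANOVA, and "Patient gender, surgery type were compared by Chi-square analysis". Drug consumption is listed with these characteristics. VAS and NRS pain are compared by repeated-measures ANOVA, with no covariate or further factor mentioned. The same section sizes the trial on this basis: "The expected standard deviation of means was 15 mm h, and standard deviation of subjects was 45 mm h of VAS". With alpha at 0.05 and a target power of 0.80, it arrives at 30 per arm.

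**The concern.** Three different cancer operations and a 55-year age span are pooled, and pain may well differ between them whatever the dose. Blocking on enrolment order balances arm sizes over time and nothing else, so the analysis is the only place left to use these factors. As written, the protocol gives them a test of between-arm difference and no role in the pain comparison.

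That test does no useful work. Under proper randomisation a baseline difference is due to chance, so its P value answers no open question. It does not show whether the difference matters for pain, and the protocol attaches no action to the result. Including a prognostic factor in the pain model does help: it removes explained variation from the error term and allows for whatever imbalance has occurred.

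At stake is power. The planned size leaves no margin above 0.80, so a gain needing no extra patients or data is worth taking.

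**Working it through.** **Inputs from the protocol (Statistical analysis; Randomization).** Three arms; 30 per arm; alpha 0.05; target power 0.80; SD of the group means 15 mm h; "standard deviation of subjects was 45 mm h of VAS".

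**Assumed input.** R², the share of pain variance explained by operation type, age and sex. The protocol gives no value. A range of 0 to 0.20 is shown, including the low end.

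**Step 1: reproduce the stated size.** One-way ANOVA, with the SD of the means taken with divisor 3:

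- f = 15/45 = 0.333, so f² = 1/9
- noncentrality λ = 3 × n × f²
- numerator df = 2; error df = 3n − 3

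At n = 30, λ = 90/9 = 10 and error df = 87, giving power 0.801. At n = 29, power is 0.786. The smallest n reaching 0.80 is therefore 30, as the protocol states.

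**Step 2: add covariates.** Operation type with three levels takes 2 df, age (linear) 1 and sex 1, four in all, so error df = 87 − 4 = 83. The residual SD becomes 45 × √(1 − R²), and λ = 10/(1 − R²).

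| R² (assumed) | Residual SD (mm h) | λ | Power at 30 per arm |
|---|---|---|---|
| 0 | 45.0 | 10.00 | 0.800 |
| 0.05 | 43.9 | 10.53 | 0.821 |
| 0.10 | 42.7 | 11.11 | 0.843 |
| 0.15 | 41.5 | 11.76 | 0.864 |
| 0.20 | 40.2 | 12.50 | 0.885 |

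To two decimals the last power is 0.88 (0.8846).

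**Step 3: the cost if the factors predict nothing.** 0.8011 − 0.8004 = 0.0007 of power. With five covariate df, for instance if a fourth kind of operation were enrolled, power at R² = 0 is 0.8002, so the loss is still under 0.001.

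**Step 4: is adjustment safe?** Under Blind, the allocation stays sealed until 30 minutes before the end of surgery. Age, sex and operation type are fixed by then and cannot be affected by the arm. Drug consumption is less clear. It is listed straight after anaesthesia and surgery duration, which suggests intraoperative drugs. The total PCA dose, however, is a secondary outcome under Observation and record, and the wording does not exclude it.

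**Limit of the calculation.** It concerns a one-way F test on a single mm h summary per patient, the scale on which the trial was sized. The planned pain test is a repeated-measures ANOVA, whose power was not computed with or without covariates.

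**The case against.** **The covariate list may belong to the statistical analysis plan.** This stands in part. Such a plan may exist and is not shown, so a reader should not infer that the factors are never used. The document shows only that the protocol's stated pain analysis names none. The baseline tests, however, are written into the protocol, and the suggested model needs only data it already collects.

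**Nothing is invalid.** This stands. A reader might infer that chance imbalance biases the dose comparison. It does not: randomisation protects the type I error, and the standard error of the unadjusted difference already reflects such imbalance. Nor is a stratification factor omitted from the analysis, since none of these factors was a stratum.

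**Imbalance can be made to look alarming.** Assuming three equally frequent operations and 30 per arm, some operation differs by at least 20 percentage points between some two arms in about 54% of randomisations. That is a maximum over nine comparisons (three operations by three pairs of arms). For one given operation and one given pair, the figure is about 13%. The consequence is also modest. If operation type explained 10% of the variance, with equally spaced means and equal shares, a 20-point swap between adjacent operations would move an arm difference by about 3.5 mm h. The standard error of that difference is 45 × √(2/30) = 11.6 mm h. The case should not rest on the 54%.

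**The gain is assumed.** This stands. At R² = 0.02, power is only 0.809. But the recommendation does not need a high R², because adjusting costs almost nothing if the factors are not prognostic.

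**Drug consumption may simply mean intraoperative drugs.** This stands too. The text does not support calling it a misplaced outcome; it supports only asking for clarification.

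**Conclusion.** The point holds as a nearly free improvement. As the protocol is written, operation type, age and sex are recorded and tested between arms, while the stated pain analysis names no covariate and the randomisation balances none of them. The result is a possible loss of precision. It is neither a bias nor an error in the sample size, which reproduces at 30 per arm.

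The possible gain runs from nil at R² = 0 to about 8 percentage points of power at R² = 0.20 (0.80 to 0.88). It rests on an assumed R², on the one-way F basis of the sample-size statement, and on the SD of the means having been taken with divisor 3, which the reproduction of 30 supports. The part that needs no assumption about R² is the cost: under 0.001 of power.

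**What to change.** 1. Before unblinding, prespecify operation type (categorical), age and sex as covariates in the primary pain model, alongside arm and time. If a statistical analysis plan already does so, align the protocol wording with it. Fixing the list in advance also prevents covariates being chosen from the baseline P values.
2. Present baseline characteristics descriptively by arm, and drop the ANOVA and chi-square P values for them.
3. State what the drug-consumption item covers. If it is intraoperative drugs, describe it as such. If it is pump use, report it as an outcome and do not adjust for it.

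The cost is a change of wording and four of the 87 error degrees of freedom. No patients, measurements or procedures are added.

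### The protocol does not say whether VAS or NRS decides the primary pain comparison, although the sample size is set on VAS alone

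*Protocol*

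**What the plan says.** Four places in the protocol bear on this point.

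- **Observation and record, primary outcome measures.** The entry is a pain scale, with no scale, time-point or summary measure named.
- **Observational measures, clinical measures.** Both scales are collected: "The clinical outcomes include pain scores VAS and NRS at each time-point". The Appendix describes each as a 0 to 10 rating of pain with the same end anchors.
- **Statistical analysis, method and threshold.** The only sentence on analysing pain is "Comparisons of VAS or NRS for pain were performed with repeated-measures ANOVA". The section closes with a threshold for all its tests: "Probability values under 0.05 were considered significant".
- **Statistical analysis, sample size.** Here only one scale appears: "The expected standard deviation of means was 15 mm h, and standard deviation of subjects was 45 mm h of VAS". The section continues "The significance level was set at 0.05 and the power at 0.8" and concludes "Then the calculated sample size was 30 patients each group".

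The sizing sentence is the only sign that VAS has priority. The analysis sentence does not carry it through.

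**The concern.** Naming the primary outcome is the protocol's task. This protocol takes the task on but leaves two candidates in place. A later analysis plan could narrow the choice, but the protocol text would still allow either scale.

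Two things are at stake.

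- **Error rate.** If the scale can be settled after both results are known, the chance of a false claim of a dose effect exceeds the 5% used in the design.
- **Interpretation.** Suppose VAS gives p = 0.04 and NRS p = 0.07, or the reverse. The protocol does not say what has then been shown. The stated aim is to find the optimal dose of an opioid, so the primary pain comparison supports a dosing conclusion.

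**Working it through.** **Inputs**

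| Input | Value | Source |
|---|---|---|
| Arms and ratio | 3 arms, 1:1:1 ("2 patients in each block assigned to A treatment, 2 assigned to B treatment and 2 assigned to C treatment") | Protocol, Randomization |
| SD of the group means | 15 mm h of VAS | Protocol, Statistical analysis |
| SD between subjects | 45 mm h of VAS | Protocol, Statistical analysis |
| Significance level, power | 0.05, 0.8 | Protocol, Statistical analysis |
| Patients per group | 30 | Protocol, Statistical analysis |
| VAS-NRS correlation | 0.7 to 0.99 | Assumed; the protocol gives none |

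**Step 1: reproduce the sample size.** For a three-group one-way F test:

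- Effect size f = 15/45 = 0.333.
- Noncentrality = 3n × f². At n = 30 this is 90 × (1/9) = 10.
- Degrees of freedom are 2 and 3(n − 1) = 87.
- Power from the noncentral F distribution at level 0.05 is 0.801.

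Thirty is the smallest n per group that reaches 0.80, so the stated figure reproduces. This takes the SD of the means with divisor 3. With divisor 2, 45 per group would be needed and power at 30 would be 0.617, so divisor 3 is evidently what was used. The calculation allows for one test, on one scale, at 0.05.

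**Step 2: upper bound if either scale is accepted.** For two independent tests at 0.05, the chance of at least one false positive is 1 − 0.95² = 0.0975, or 9.75%.

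**Step 3: correlated scales.** Both scales rate the same pain in the same patients, so independence is unrealistic. Two correlated three-group F tests were simulated under no dose effect, with 30 per group, one summary score per scale and each test at 0.05. The chance that at least one is significant is:

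| Assumed correlation | Type I error if either counts |
|---|---|
| 0.70 | 8.4% |
| 0.80 | 7.9% |
| 0.90 | 7.1% |
| 0.95 | 6.5% |
| 0.99 | 5.7% |
| 1.00 | 5.0% |

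Repeat simulations with 200,000 or more runs per correlation agree to about 0.1 percentage point. The rate returns to 5% only when the scales carry identical information.

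**Step 4: cost of the remedies.**

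- One scale named primary: level 0.05, 30 per group, power 0.801. Nothing changes.
- Both scales kept, with success on either counting and each tested at 0.025 (Bonferroni): power at 30 per group falls to 0.711. Restoring it takes 36 per group (power 0.804), which is 3 × 6 = 18 more patients.

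**The case against.** **No success rule is stated.** A reader might infer that the protocol declares success when either scale reaches p < 0.05. It does not. The 0.05 sentence is a general threshold in a paragraph that also covers baseline comparisons and ranked data. The analysis sentence can be read as matching a method to a type of variable, as the sentence after it does. This objection stands: what can be supported is that the deciding scale is left open, so the error rates above are conditional on either scale being accepted.

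**More than two chances.** A reader might also count the group effect and the group-by-time effect on each scale and arrive at four chances. The documents do not support putting a figure on that. They list no time-points and give no covariance structure, and the choice of model term is commonly left to an analysis plan. That count forms no part of this point.

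**VAS is implied.** The sizing sentence names only VAS, so a careful reader might treat VAS as primary. This limits the practical freedom and lowers the severity. It does not remove the gap, because neither the outcome list nor the analysis sentence says so.

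**The inflation is small.** Two ratings of the same pain with the same anchors plausibly correlate highly, and at 0.99 the excess is under one percentage point. That is fair. However, the undefined meaning of a split result does not depend on how large the inflation is.

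**Conclusion.** The point holds in a limited form. The primary pain scale is not named, two scales are collected and both come under the pain analysis at 0.05, while the trial is sized on one. The text permits the primary result to come from either.

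If either is accepted, the type I error of the group comparison is about 5.7% to 8.4% instead of 5%, an excess of roughly 0.7 to 3.4 percentage points. This rests on an assumed correlation of 0.99 to 0.7 and on one between-group test per scale. Severity: should be fixed. The inflation is modest and the sizing already points to VAS, but the primary comparison cannot be interpreted unambiguously until one scale is named.

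**What to change.** Make two changes to the protocol text.

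1. In the list of primary outcome measures, replace the general entry with VAS pain as the only primary pain scale, summarised as time-integrated VAS in mm h. The unit in the sizing sentence implies this quantity. State the time-points over which it is integrated, and that the 10 cm line is converted to millimetres.
2. In Statistical analysis, replace the either-scale wording with one primary test: a three-group F test of that summary at 0.05. State that NRS and the repeated-measures ANOVA results are supportive and cannot replace the primary result.

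Naming VAS without the second change would leave the tested quantity (repeated scores) different from the one used for sizing (mm h).

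The cost is wording in two places. No extra patients or measurements are needed, and power stays at 0.801 with 30 per group. The small downside is that a significant NRS result alone could no longer be claimed as the primary finding.
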